### Outcome measures

#### Baseline data

The demographic data of all participants (gender, age, height, weight, country, nationality and occupation, etc.) and clinical characteristics (including type and location of damage, current pain level) will be recorded with an internally designed form at baseline (T0, 2 min before the intervention). Vital signs such as blood pressure (BP), heart rate (HR), and oxygen saturation (SPO_2_) will also be collected at baseline.

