### Participants

All patients who received MT after ACL reconstruction facing acute pain will be invited to participate in this study. To decrease confounding factors that may interfere with pain scores during the rehabilitation, we will recruit patients with relatively consistent surgical site as much as possible (unilateral joint). The inclusion criteria are as follows: willing to participate in the trial and sign informed consent; man or woman; age ≥ 18 years old; patients underwent primary unilateral ACL reconstruction (1 month post-operative, with or without meniscal injury or collateral injury); experience worst pain (during MT) was reported ≥ 4 (on a visual analogue scale (VAS) of 0–10 cm); without postoperative complication. Exclusion criteria include the following: patients with pain unrelated to MT; patients who have undergone other surgical operations on the knee except for ACL; mental disorder or altered mental status have difficulty in reporting pain; patients with contraindications to N_2_O (abdominal distension or suspected bowel obstruction, air embolism, pneumothorax, decompression sickness, epilepsy, pulmonary cancer, chronic obstructive pulmonary disease and acute respiratory infection, pregnancy, severe inhalation injury, pharmaceutical or pathological pulmonary fibrosis, maxillofacial injuries, disease involving ear, nose, larynx, such as sinuses, otitis media); drug dependence or abuse. The main inclusion and exclusion criteria are presented in Table 2.

**Table 2 Tab2:** Main inclusion and exclusion criteria

**Inclusion criteria**	**Exclusion criteria**
Patients with acute pain caused by manual treatment after anterior ligament reconstruction	Patients with mental disorder or altered mental status have difficulty in reporting pain
Age ≥ 18 years old	Patients who have undergone other surgical operations on the knee except for ACL
Willing to participate in the trial and sign informed consent	Drug dependence or abuse
Background worst pain (during Manual therapy) reported being 4 or higher (on a visual analogue scale (VAS) of 0 to 10 cm)	Contraindications to N_2_O (suspected bowel obstruction, air embolism, pneumothorax, epilepsy, chronic obstructive pulmonary disease, and acute respiratory infection, pregnancy, pharmaceutical or pathological pulmonary fibrosis, maxillofacial injuries, disease involving ear, nose, larynx)
Without postoperative complication	

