### Intervention

After inclusion in the study, participants will be randomized into intervention and control groups. All procedures will be carried out in the rehabilitation treatment hall. MT includes passive joint movement and joint stretching for a total of 30 min. The procedure is performed by qualified rehabilitation therapists who have worked for more than 2 years in the hospital. And the two gases implemented are conducted by trained and qualified nurses. Before and after the MT, wax therapy, and cold compress are applied as routine treatments. The patients in the intervention group began inhaling pre-mixed 65% N_2_O through a specially designed mask with a check valve, 2 min before MT, and continue the whole procedure until it ends, while the control group inhaled 100% oxygen under the same conditions. The gas will be administered by the patients themselves in order to observe their state of consciousness. Blood pressure will be measured before, during, and after each MT, and the oxygen saturation and heart rate were continuously monitored with a pulse oximeter throughout the process. Image and audio recordings will be taken individually for communication coding and data analysis. Adjuvant analgesics will also be recorded.

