#### Primary outcome

The primary outcome measure will be the degree of pain assessed on the VAS (a patient self-assessment scale) at T0, T1 (5 min after the beginning of the intervention), and T2 (5 min after the intervention finished), respectively. The time point selection was based on the pharmacokinetics of N_2_O. The VAS is a horizontal line without numbers or verbal descriptors at intermediate points, ranging from 0 to 10 cm (0: no pain; 10: worst imaginable pain). The VAS is chosen due to its simplicity, adaptability to a broad range of populations, and more important, it has good visual properties [24].

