### Sample size estimates

A prospective sample size estimate was conducted by a senior statistician using the GPower 3.1 procedure during the protocol-writing stage. The level of pain relief is regarded as the primary endpoint measure of this trial [27]. To achieve a statistical power of 80% (*β* = 0.20) and two-tailed testing (at a type-1 error rate of 5%) is sufficient. Based on the pre-trial with 20 patients (Corr among rep measures = 0.602), a sample size of 12 was targeted as being sufficient to achieve the required effective sample size, but to meet the Chinese Food and Drug Administration standard for the safety and feasibility of nursing staff implementing this inhalation analgesic, the targeted sample size of 120 was recommended.

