## Limitation

Some limitations must be acknowledged in this study. Firstly, the pain score was the subjective outcome and was not consistently assessed by individual patients; therefore, it is susceptible to the subjective influence of patients. Secondly, data extraction is only during and after the procedure, without long-term effect records.

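### The baseline pain score (T0) precedes manual therapy, and the qualifying score for pain during therapy is not scheduled as baseline data: T0-to-T1 change is not pain relief, and some precision is given up

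*Protocol article*

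**What the plan says.** **Eligibility.** Under Participants, a patient qualifies if "experience worst pain (during MT) was reported ≥ 4 (on a visual analogue scale (VAS) of 0–10 cm". Table 2 has the same criterion: "Background worst pain (during Manual therapy) reported being 4 or higher".

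**Baseline.** Under Baseline data, the "current pain level) will be recorded with an internally designed form at baseline (T0, 2 min before the intervention". The lists there do not name the qualifying score, and Table 1 has no pain score in its enrolment column.

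**Timing of gas and therapy.** Under Intervention, patients start inhaling "2 min before MT, and continue the whole procedure until it ends".

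**Endpoint.** Under Primary outcome, "The primary outcome measure will be the degree of pain assessed on the VAS (a patient self-assessment scale) at T0, T1" and T2. T1 is five minutes into the intervention and T2 five minutes after it ends. Under Sample size estimates the wording differs: "The level of pain relief is regarded as the primary endpoint measure of this trial". Relief is not defined there and no reference time is given.

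**Analysis.** Data management and analysis names two-group t-tests or rank tests for quantitative data. It mentions neither a covariate nor a change from T0.

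**The concern.** The trial asks whether nitrous oxide lowers pain during manual therapy. Relief implies a reference score, and T0 is the only pre-treatment pain score on the schedule. T0 describes a patient not yet being treated, while T1 describes a patient under treatment. The criteria select people whose pain is provoked by therapy and exclude pain unrelated to it, so a lower score at T0 than at T1 is likely in both arms. A within-arm change could then show worsening even if the gas works.

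The one pre-treatment score that describes pain during therapy must be obtained to apply the inclusion criterion, but the schedule does not list it as data. Unless it is reported and used, a chance difference between the arms in how painful therapy is goes unseen, and variation that could be explained stays in the error term.

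**Working it through.** **The plan's own figure.** The calculated sample size of 12 cannot be reproduced, because the article gives no effect size, SD or named test. Nothing below depends on it.

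**1. Where each score falls.** The word intervention could mean the gas or the therapy. Gas starts 2 min before therapy.

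| Reading | T0 | T1 | T2 |
|---|---|---|---|
| Intervention = gas | 2 + 2 = 4 min before therapy | 5 − 2 = 3 min into therapy | after therapy |
| Intervention = therapy | 2 min before therapy | 5 min into therapy | after therapy |

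On either reading T0 precedes therapy, and only T1 lies within it.

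**2. Within-arm change against between-arm difference.** Assumed scores, for illustration: T0 = 2 in both arms; T1 = 6 on oxygen and 4 on nitrous oxide.

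- Change T1 − T0: oxygen 6 − 2 = +4; nitrous oxide 4 − 2 = +2. Pain rises in both arms.
- Between-arm difference at T1: 4 − 6 = −2.
- Between-arm difference in change: 2 − 4 = −2.

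The last two agree because randomisation gives T0 the same expected value in each arm. The within-arm reading fails; the treatment comparison does not.

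**3. Precision of T1 alone, change from T0, and T0 as covariate.** With 60 per arm, two-sided 5% and 80% power, the detectable difference in SD units is (1.960 + 0.842) × √(2v/60). Here v = 1 for T1 alone, 2(1 − ρ) for change and 1 − ρ² with T0 as covariate, where ρ is the T0–T1 correlation and the SDs are equal.

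| ρ | T1 alone | Change from T0 | T0 as covariate |
|---|---|---|---|
| 0 | 0.511 | 0.723 | 0.511 |
| 0.2 | 0.511 | 0.647 | 0.501 |
| 0.4 | 0.511 | 0.560 | 0.469 |
| 0.602 | 0.511 | 0.456 | 0.408 |

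The value 0.602 is the repeated-measures correlation from the 20-patient pre-trial; the article does not say which time points it refers to. The other values are assumed. Change from T0 is less precise than T1 alone when ρ is below 0.5, and covariate adjustment is no worse than either in any row.

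**4. Further gain from the qualifying score.** Let r be its partial correlation with T1 given T0. The documents do not give r. The ratio of interval widths is √(1 − r²).

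| r (assumed) | √(1 − r²) | Interval narrower by |
|---|---|---|
| 0.1 | √0.99 = 0.995 | 0.5% |
| 0.2 | √0.96 = 0.980 | 2.0% |
| 0.3 | √0.91 = 0.954 | 4.6% |
| 0.5 | √0.75 = 0.866 | 13.4% |

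**The case against.** **No harm to the main question.** The stated aim is less pain than with oxygen, and the planned tests compare arms. The illustration itself returns the full 2 cm effect from T1 alone or from change. This stands. A reader might infer that the trial cannot measure relief of therapy pain at all, or that relief is defined as change from T0. The documents support neither: relief is left undefined, and no analysis of change is stated.

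**Silence is not disposal.** A reader might infer that the qualifying score is discarded. No section says so. The baseline lists are open-ended, and the full case report form may hold the score. That stands against any claim of loss. It does not alter the fact that Table 1 and Baseline data say which pain scores are recorded and when, and this one is not among them. The remark under Limitation that "data extraction is only during and after the procedure" adds nothing, since that sentence concerns missing long-term records.

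**Covariates belong to the SAP.** Often so, and an SAP not shown may adjust. But the article does state its between-group tests, and they are unadjusted.

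**The gain may be small.** This also stands. The qualifying score is a worst score restricted to 4 or more, with no stated recall period, whereas T1 is a single moment early in therapy. Both features would tend to weaken the correlation, so the lower half of the range is as plausible as the upper.

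**The score would be a poor reference.** Correct. Patients are selected for a high peak value, so regression to the mean would produce apparent relief even on oxygen. This rules it out as a reference for change, but not as a covariate, where the selection applies to both arms alike.

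**Conclusion.** The concern holds in a limited form. T0 and T1 describe different pain states on either reading of the timings, so a within-arm T0-to-T1 change should not be reported as pain relief. The randomised comparison at T1 is unbiased and addresses the trial's question.

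The cost is in precision and in the ability to see chance imbalance in pain during therapy. Beyond what T0 explains, using the qualifying score would narrow the interval by about 0.5% to 2% if the partial correlation is 0.1 to 0.2, and by about 5% to 13% if it is 0.3 to 0.5. These correlations are assumptions; the documents contain no figure for them. The change is worth making because it is nearly free, not because the trial fails without it.

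**What to change.** 1. Add the qualifying score for worst pain during therapy, with its date, to Baseline data and to the enrolment column of Table 1. Report it by arm.
2. In Data management and analysis, compare VAS at T1 between arms with T0 and the qualifying score as covariates. Fix this before unblinding.
3. In Sample size estimates, replace the level of pain relief with the between-arm comparison of VAS during manual therapy, in line with Primary outcome.
4. Keep T0 as a separate pre-therapy score, and do not describe T0-to-T1 change as relief. Do not use the qualifying score as a change-from-baseline reference either.

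The cost is one data field, a model term and some wording; no extra patients or visits are needed. There are two small drawbacks. The recall period of the screening score may differ between patients. Its value must also be recoverable from the screening records of those already enrolled, who numbered 98 of the planned 120 when the article was written.

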#### Primary outcome

The primary outcome measure will be the degree of pain assessed on the VAS (a patient self-assessment scale) at T0, T1 (5 min after the beginning of the intervention), and T2 (5 min after the intervention finished), respectively. The time point selection was based on the pharmacokinetics of N_2_O. The VAS is a horizontal line without numbers or verbal descriptors at intermediate points, ranging from 0 to 10 cm (0: no pain; 10: worst imaginable pain). The VAS is chosen due to its simplicity, adaptability to a broad range of populations, and more important, it has good visual properties [24].

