## Abstract

**Background:**

Many patients during manual therapy after anterior ligament reconstruction will experience severe pain, which has a negative impact on their rehabilitation. However, there is rarely an analgesic method for these patients during rehabilitation. Nitrous oxide with rapid analgesic and sedative effects is often used to relieve pain in minor procedures. The purpose of this study is to determine whether or not nitrous oxide analgesia decreases pain compared to oxygen during manual therapy after anterior ligament reconstruction.

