Oral or intravenous analgesics are usually used for immediate to short-term postoperative pain, but there is no systematic rehabilitation period analgesia program through literature review. Commonly used drugs include systemic opioids, non-steroidal anti-inflammatory drugs, and gabapentinoids [10, 11]. Although they can alleviate pain, it has many side effects concurrently, such as nausea and vomiting, lethargy and over-sedation, respiratory depression, and gastrointestinal tract damage [12]. These side effects may lead to delayed recovery after anesthesia or early postoperative recovery, increasing the length of stay and reducing patient satisfaction. Nitrous oxide (N_2_O), as an analgesic and sedative, which has the advantages of simple handling, fast onset, good effect, and few adverse reactions, is commonly used in various painful procedures [13]. Different studies have reported that the use of N_2_O can bring about notable pain relief in different areas of medicine such as minor dental surgery, emergency trauma, labor analgesia, plastic operation, colonoscopy, cancer pain, bone marrow biopsy, and invasive operation in pediatrics [14–21]. It usually produces effective and transient analgesia without changing consciousness and cognition, so patients can soberly cooperate with therapists during treatment. The device is portable and cheap, and patients can control it easily. It was observed that all side effects (dizziness, euphoria, nausea, vomiting, etc.) were temporary and disappeared within 5 min after stopping inhalation. No serious complications were found [22, 23].

There is an absence of a trial assessing the efficacy of N_2_O with MT after ACL reconstruction surgery. It is required that reasonable analgesia for patients who underwent MT. Thus, the purpose of this study is to evaluate the analgesic effect of inhaling N_2_O during rehabilitation on patients receiving MT through a randomized double-blind controlled trial. We hypothesized that its analgesic properties would decrease pain compared to placebo during MT with few side effects.

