### Data management and analysis

Data are treated confidentially. To improve the quality of data collection, all researchers will receive professional training before the study. All study-related information (e.g., data collection forms/digital files) will be stored securely in the medical office. Personally identifiable information of participants, such as names, and gender, will be replaced by codes throughout the study and will always remain confidential, with only the project manager or relevant doctors aware of the patient’s personal information.

And any public reports on the results of this study will not reveal any identifiable information about the patient. Composition of data monitoring committee (DMC) and auditing system will be established shortly after the project launch to monitor the collection and management of data and patient safety throughout the study. Members will include four professional therapists and nurses, two pain management specialists, and a senior academic statistician who worked as the board’s chair.

A double data check has also been performed for quality control. According to the data collection methods and criteria developed by the project leader and professionals, all data will be recorded carefully and comprehensively to ensure the authenticity of the data. Missing data on withdrawn participants will be imputed using the multiple imputation method.

All statistical analyses will be performed by SPSS version 25 (IBM Inc, Armonk, New York), with an alpha set at 0.05. Statisticians will calculate the mean (standard deviation), median (interquartile range), minimum, maximum, and proportion (95% confidence interval) for quantitative data and describe numbers and percentages for qualitative data. The mean will be compared by Student’s *t*-test (normal distribution parameter) or nonparametric two-sample Mann–Whitney test (nonnormal distribution parameter). The proportions will be compared using the chi-square test or Fisher exact test. The comparisons between two groups will be performed as follows: *t*-tests or Wilcoxon rank sum (normal or nonnormal ability distributions) for quantitative data; chi-square test or Fisher’s exact test for qualitative data. The value of *P* < 0.05 will be considered statistically significant.

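### The primary outcome is VAS pain at three times with no deciding comparison named, and only T1 falls during manual therapy

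*Protocol article*

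**What the plan says.** All references are to the protocol article.

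- **Primary outcome:** "The primary outcome measure will be the degree of pain assessed on the VAS (a patient self-assessment scale) at T0, T1". Of these, T1 is set 5 min into the intervention. The third and last time is "T2 (5 min after the intervention finished), respectively". The section names no lead time point, change score or summary over time. It says that pharmacokinetics guided the choice of times.
- **Baseline data:** demographic and clinical data, including current pain, "will be recorded with an internally designed form at baseline (T0, 2 min before the intervention". The randomization section places the request for a random number after the baseline assessment.
- **Question:** the Abstract asks whether "nitrous oxide analgesia decreases pain compared to oxygen during manual therapy after anterior ligament reconstruction". The Introduction's hypothesis also concerns pain during manual therapy.
- **Intervention:** gas starts 2 min before manual therapy and runs until it ends. Manual therapy lasts 30 min.
- **Sample size estimates:** "The level of pain relief is regarded as the primary endpoint measure of this trial", with no time point, together with a correlation among repeated measures of 0.602 from a 20-patient pre-trial.
- **Data management and analysis:** t-tests or rank tests between two groups, "with an alpha set at 0.05". No repeated-measures model is given, and no rule covers more than one time point.

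**The concern.** A primary outcome has to lead to one decision. Here three measurements have equal standing, and they do not measure the same thing. T0 cannot show an effect of treatment. T2 records pain once both the painful stimulus and the gas have been withdrawn. T1 is the only listed measurement taken while both are present.

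If T1 and T2 disagree, the article gives no rule for the conclusion, so the choice could be made after the results are seen. A difference at T2 alone could be reported as a positive primary result although it does not address pain during therapy. Two unadjusted chances of success would also raise the false-positive rate above the stated 5%.

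**Working it through.** **1. Which times address the question**

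| Time | Relation to gas and therapy | Role |
|---|---|---|
| T0 | 2 min before the intervention, before allocation | Baseline |
| T1 | 5 min after the intervention begins; gas and therapy both running | Pain during therapy |
| T2 | 5 min after the intervention ends; both stopped | Pain after therapy |

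If the intervention begins with the gas, T1 is 5 − 2 = 3 min into therapy. If it begins with therapy, T1 is 5 min in. On either reading T1 lies within the 30-min session.

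**2. Whether the sample size section identifies the comparison**

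The stated size of 12 cannot be reproduced, because the effect size, the number of measurements, and whether 12 is a total or per group are not given. Take 12 as a total, 80% power, two-sided 5% and correlation 0.602. The effect size f that a two-group repeated-measures ANOVA would need is then:

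- group-by-time interaction: 0.35 with three measurements, 0.40 with two;
- between-group effect: 0.77 with three measurements, 0.80 with two.

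The quoted correlation suggests a repeated-measures calculation. It does not show which effect was meant, and the analysis section contains no such test.

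**3. Type I error if T1 and T2 are both tested**

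Inputs: two-sided 0.05 per test (analysis section), so the critical value is 1.96. The correlation ρ between the two test statistics is an assumption. The value 0.602 is borrowed from the sample size section, which does not say which measurements it relates.

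Formula: error = 1 − P(|Z1| < 1.96 and |Z2| < 1.96), with Z1 and Z2 standard normal and correlation ρ.

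| ρ | P(neither significant) | Error |
|---|---|---|
| 0 | 0.95² = 0.9025 | 9.75% |
| 0.3 | 0.9049 | 9.5% |
| 0.602 | 0.9125 | 8.7% |
| 0.8 | 0.9219 | 7.8% |

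The upper bound at any correlation is 0.05 + 0.05 = 10%.

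**4. Cost of controlling the error**

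With n = 60 per group (120 at 1:1) and 80% power, the detectable standardised difference is approximately d = (z for 1 − α/2 + z for 0.80) × √(2/n).

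- α = 0.05: (1.960 + 0.842) × √(2/60) = 0.511; with the noncentral t, 0.516, or 0.52.
- α = 0.025: (2.241 + 0.842) × √(2/60) = 0.563; with the noncentral t, 0.569, or 0.57.

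These figures are for an unadjusted two-group comparison.

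**The case against.** The strongest reply is that T0, T1 and T2 are only measurement occasions, that the quoted correlation points to one repeated-measures test, and that an analysis plan not shown may name the comparison. Part of this stands. The article never says that VAS will be tested separately at each time, so the inflated error is conditional and not a fact. The reply does not remove the defect. The primary outcome definition itself gives a baseline and a post-therapy measurement the same standing as T1, and the analysis section contains no repeated-measures test. The pharmacokinetic rationale explains why the times were chosen, not which one decides.

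The wording about pain relief may be a loose name for the VAS outcome. That is fair, and aligning the wording is enough.

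T1 is also an imperfect choice, since it samples only the first minutes of a 30-min session. That is a reason to allow T1 and T2 as co-primary with split alpha, not to leave the choice open.

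Some stronger readings are tempting, but the documents do not support them:

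- **Three routes to a claim.** A reader might count T0. It is measured before allocation, so a difference there is chance imbalance and cannot credibly support efficacy. There are two routes.
- **Analgesia has gone by T2.** The Introduction says that "all side effects (dizziness, euphoria, nausea, vomiting, etc.) were temporary and disappeared within" 5 min of stopping inhalation. That concerns side effects. The analgesia is described as short-lived, but no duration is given.
- **Cold treatment biases T2.** The Intervention section says "Before and after the MT, wax therapy, and cold compress are applied as routine treatments". It describes no difference between arms and does not place the cold compress before or after T2.

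**Conclusion.** The concern holds in a limited form. The article names no deciding comparison for its primary outcome, and one of its two post-baseline times lies outside the period the trial asks about. T2's mismatch rests on timing alone: gas and therapy have both stopped by then.

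The type I error is about 8.7%, with a range of 7.8% to 9.5%, under three assumptions: T1 and T2 are tested separately without adjustment, either one counts as success, and the test statistics correlate at 0.602 (range 0.8 to 0.3). Under a single prespecified test the error stays at 5%. The article does not specify such a test.

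**What to change.** Before unblinding, amend the protocol and update the registry entry:

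1. Make the single primary endpoint the between-group difference in VAS at T1 as already measured, adjusted for T0 (for example by ANCOVA) and tested at two-sided 0.05.
2. Use T0 only as a covariate, with no between-group test.
3. Make T2 secondary.
4. Use the same endpoint wording in the sample size section.
5. Reconcile the randomization, intervention and primary outcome sections on what marks the beginning of the intervention. The first gives 30 min of inhalation, while the second starts gas 2 min before 30 min of therapy. Record what has been done and do not move T1: the Trial status section reports 98 participants already included, and a new anchor could not be applied to them.
6. Because the Abstract describes once-daily sessions, state which session's T1 is meant.

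If the sponsor wants both T1 and T2 as primary, test each at 0.025. The total error is then at most 5%, and the detectable difference rises from 0.52 to 0.57.

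The cost is a change of wording, with no new data. The sponsor gives up T2 as an unadjusted route to a positive primary claim.
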